### Sample size calculating

The sample size for this study was calculated based on the results of a previous study conducted by the research team, which has not yet been published. A total of 66 patients participated in the previous study. It was conducted at the same hospital by the same research team and the sample size was determined using the sample size calculation formula as described in the previous study. The control group had a score of 5.6 ± 2.0 while the 10 mg dexamethasone group had a score of 6.8 ± 1.6. The significance level (*α*) was set at 0.05 and the power (*β*) at 0.10. Accounting for a dropout rate of 20%, the final sample size was calculated to be 48 cases in each group, which would require approximately 58 cases per group and 116 cases in total. The formula for calculation is as follows.$$n= \frac{{({Z}_{\alpha }+ {Z}_{\beta })}^{2} \left(1+1/k\right) {\sigma }^{2}}{{\delta }^{2}}$$

Analysis:A)When *k* equals 1, both groups have the same sample size, and *n* represents the size of each group.B)In our study, if α is 0.05 and *Z* is two-tailed, then *Z*_0.05_ is 1.96; if *β* is one-tailed and the test efficiency is 0.9, then *Z*_*β*_ equals 1.28.C)The overall variance *σ*^2^ can be estimated using the sample variance *S*^2^ in the formula.D)*δ* represents the difference between the average values of the two groups.

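### The 20% dropout allowance is attached to the wrong number and is slightly too small: 58 per group leaves about 46 evaluable, not the 48 that the formula requires

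*Protocol article*

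**What the plan says.** All of this stands in the protocol article, mostly under the heading Sample size calculating.

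- Inputs from an unpublished study of 66 patients by the same team: "The control group had a score of 5.6 ± 2.0 while the 10 mg dexamethasone group had a score of 6.8 ± 1.6".
- Error rates: the critical value is 1.96, "if α is 0.05 and *Z* is two-tailed"; the value for β is 1.28, where β "is one-tailed and the test efficiency is 0.9".
- Allocation: k = 1, so "both groups have the same sample size".
- Result: "Accounting for a dropout rate of 20%, the final sample size was calculated to be 48 cases in each group". The same sentence then raises this to about 58 a group, 116 altogether.

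The formula is printed and contains no dropout term. The step from 48 to 58 is not shown. The abstract repeats 58 per group, and the section on randomization and blinding fixes 116 sealed envelopes. Under Rejection criteria, patients who withdraw, cannot complete the sleep and cognitive assessments, or have a second operation are taken out of the study.

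**The concern.** Two things in the result sentence do not fit together. As worded, 48 already includes the dropout allowance, yet the sentence goes on to a larger number, 58, without giving another reason for it. And if 48 is the number needed for analysis, 58 does not leave 48 after the stated loss.

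What is at stake is a declared design property: 90% power after 20% dropout. Patients who drop out are removed from the study, so the number that remains determines the power. The wording could also lead a reader to think that enrolling 48 per group is enough.

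**Working it through.** **Inputs (Sample size calculating).** δ = 6.8 − 5.6 = 1.2. SDs 2.0 and 1.6. Zα = 1.96, Zβ = 1.28, k = 1. Dropout 20%. The section says only that the sample variance estimates σ². Equal-weight pooling of the two variances is therefore my assumption: σ² = (4.00 + 2.56)/2 = 3.28, SD 1.811.

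**Step 1: reproduce the 48.**
n = (1.96 + 1.28)² × (1 + 1/1) × 3.28 / 1.2² = 10.4976 × 2 × 3.28 / 1.44 = 47.8, so 48 per group. With the SD rounded to 1.8, the result is 47.2, again 48. The stated figure is reproduced with no dropout in it.

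**Step 2: reproduce the 58.**
48 × 1.2 = 57.6, so 58 per group and 116 in total. This matches the protocol. Division by 0.8 gives 60, which does not.

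**Step 3: what a 20% loss requires.**
A 20% loss leaves 80% of those enrolled, so n = 48 / (1 − 0.20) = 60 per group, 120 in total. The plan is short by 2 per group, 4 in total.

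**Step 4: what 58 delivers.**
58 × 0.8 = 46.4, so about 46 per group. The loss that 58 can absorb while keeping 48 is 1 − 48/58 = 17.2%.

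**Step 5: power, each method compared with itself.**
Normal approximation (the protocol's method): power = Φ(δ / (σ√(2/n)) − 1.96).
- n = 48: 1.2 / (1.811 × 0.2041) = 3.246; Φ(1.286) = 90.1%.
- n = 46: 1.2 / (1.811 × 0.2085) = 3.178; Φ(1.218) = 88.8%.

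| Evaluable per group | Normal, SD 1.811 | Normal, SD 1.8 | Noncentral t, SD 1.811 |
|---|---|---|---|
| 48 | 90.1% | 90.4% | 89.5% |
| 46 | 88.8% | 89.2% | 88.2% |

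The loss is 1.2 to 1.3 percentage points whichever column is used.

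**Sensitivity to the SD.** With SD 2.0 alone, the formula gives 58.3, so 59 per group before dropout. With SD 1.6 alone, it gives 37.3, so 38.

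**The case against.** The best case on the other side is that this hardly matters. Power falls by little more than one point, the text says the 58 is approximate, and the choice of SD moves the required number from 38 to 59 per group, far more than the 2 patients at issue. All of that stands, and it limits how much weight the point can carry. It does not make the figure right: a required number is rounded up, and the abstract and the envelope count treat 58 and 116 as fixed.

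It can also be said that the multiplication by 1.2 is inferred. That is correct, but the shortfall does not depend on it. However 58 was reached, a 20% loss from it leaves fewer than 48.

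A third defence takes the sentence literally. With SD 1.6 alone, 38 / 0.8 = 47.5, so 48 would already include dropout. The further step to 58 would then have no explanation, and the control group's larger SD would have been ignored. Pooling explains both stated numbers.

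Two stronger readings are tempting, and the document supports neither.

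- A reader might set the t-test power at 46 (88.2%) against the nominal 90% and report a loss of 1.8 points. Part of that comes from changing method: on the t-test, 48 per group already gives only 89.5%, and 49 would be needed for 90%.
- A reader might infer that the rejection criteria cause losses on top of the 20%. Withdrawal and missing assessments are what a dropout allowance ordinarily covers, and nothing says that the 20% leaves out any of the three criteria. Adding them could count the same patients twice.

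**Conclusion.** The point holds as a minor error in a stated design figure. The 48 is the evaluable number before dropout, and the sentence wrongly attaches the allowance to it. The allowance then added covers about 17% dropout, not 20%. At 20%, about 46 per group remain, and power by the protocol's own formula is about 89%, not 90%.

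This rests on equal-weight pooling of the two SDs, which reproduces the stated 48, and on dropouts leaving the analysis, as the rejection criteria provide. It does not show a trial that is materially underpowered on its own assumptions, and it casts no doubt on the validity of the comparison.

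**What to change.** Keep 116 patients and restate the result under Sample size calculating along these lines: *48 evaluable patients per group are required for 90% power; 58 per group (116 in total) allows for about 17% dropout; at 20% dropout (46 per group) power is about 89% by the same formula.* It would help to add that the variance is the equal-weight average of the two sample variances, if that is what was done. The cost is one sentence, a slightly less favourable stated figure and no extra patients.

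If the sponsor prefers to keep both 20% dropout and 90% power, the figures become 60 per group and 120 in total. At 20% loss that leaves 48 per group and 90.1% power by the normal approximation. It costs four more patients and a change to the abstract and to the number of randomization envelopes.

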### Randomization and blinding

In order to mitigate selection bias, randomization and allocation concealment were conducted by a medical statistician prior to the commencement of the trial. The patients were randomly assigned to two groups in a 1:1 ratio using SPSS 26.0: the dexamethasone group (group D) and the control group (group C). Post-randomization information was sealed in 116 brown paper envelopes and stored in sequence in cabinets. On the day of surgery, the envelopes were opened in sequence based on group assignment and read by an anesthesia nurse on the research team. Dexamethasone or saline was prepared based on the randomization. An anesthesiologist who was blinded to the group assignments conducted the trial. A specialized anesthesiologist performed the outcome assessment, while another anesthesiologist carried out the data analysis. Both of them were unaware of the group allocations. Details regarding patient recruitment advertisement can be obtained from the corresponding author. [name], a valued member of the research team, assumes the pivotal role of patient recruitment. [name] diligently arranges a preoperative visit with the patient the day prior to their scheduled surgery. During this essential preoperative encounter, her primary objective is to ensure that the patients possess a thorough understanding of the study and the clinical significance of their participation, while also obtaining their signed informed consent for the trial.

We will request consent for review of participants' medical records, and for the collection of blood samples to assess Hemoglobin, albumin, serum sodium, testosterone, cortisol, IL-6, TNF, NSE, and Sβ-100 were recorded before surgery, 1 day and 2 day after surgery. The patient's blood specimens will be collected by dedicated laboratory personnel. After proper processing, these samples will be stored in an ultra-low temperature freezer at − 80℃ for subsequent molecular biology experiments and surveillance.

### Experimental process

Before surgery, all recruited patients scheduled for elective robot-assisted radical prostatectomy were selected based on the inclusion criteria mentioned above, assessed using the PSQI scale, and screened for eligibility based on the exclusion criteria mentioned above. Standardized perioperative management and postoperative care process were uniformly implemented for the enrolled patients, which included preoperative preparation according to the standard surgical routine. The general flow chart and trial schedule are displayed in Fig. 1 and Table 1, respectively.

**Fig. 1 Fig1:**
[figure not shown]
Presents a flowchart depicting the impact of dexamethasone on the quality of postoperative sleep and the incidence of postoperative delirium in elderly patients who have undergone radical prostatectomy

**Table 1 Tab1:** Schedule

Events	Time						
	Preoperative			Intraoperative		Postoperative	
	*T*_0_		*T*_2_	*T*_3_	*T*_4_	*T*_6_	*T*_7_
**Enrollment**							
Eligibility screening		**X**					
Informed consent		**X**					
Random allocation		**X**					
**Interventions**							
Dexamethasone			**X**				
Normal saline			**X**				
**Data collation**							
Baseline variables		**X**	**X**	**X**	**X**	**X**	
Follow-up results						**X**	**X**
Case report form		**X**	**X**	**X**	**X**	**X**	**X**
Relevant test data		**X**					**X**
**Assessments**							
PSQI scale		**X**					
MMSE scale		**X**					
AIS scale		**X**					**X**
CAM scale							**X**
Blood test indexes		**X**				**X**	
Postoperative complications						**X**	**X**

T_0_: before admission to the operating room; T_2_: induction of anesthesia; T_3_: beginning of surgery; T_4_: end of surgery; T_6_: in the recovery room after the operation; T_7_: within 72 h after operation

Patients will be required to abstain from food and alcoholic beverages on the day of surgery. Upon admission, a venous access will be established for the patient and vital signs are monitored, including electrocardiogram (ECG), heart rate (HR), pulse oxygen saturation (SpO_2_), and invasive blood pressure (IBP), using radial artery catheterization. The test group received dexamethasone 10 mg/5 ml during induction, while the control group received normal saline 5 ml. Patients will be received pre-administered oxygen at 6 L/min, with an inspired oxygen concentration of 100%. Induction was achieved rapidly using intravenous bolus doses of propofol 1 ~ 3 mg/kg, sufentanil 0.3 ~ 0.5 μg/kg, and cis-atracurium besylate 0.2 mg/kg was rapidly induced, after the patient had lost consciousness and the muscle was fully relaxed. The trachea will be then intubated under visualization by the same attending anesthesiologist and confirmed to be in position. The anesthetic machine will be used for mechanical ventilation, and respiratory parameters were adjusted to maintain an oxygen concentration of 100% and an end-respiratory carbon dioxide level of 35 ~ 45 mmHg throughout the surgery. Appropriate muscle depth will be maintained throughout the surgery by continuous infusion of propofol 3 ~ 5 mg/(kg h)^−1^ and remifentanil (0.1 ~ 0.3 µg/(kg min)^−1^). Intravenous cisatracuride will be administered 30 min before the end of surgery, and a static push of sufentanil 0.1 ~ 0.2 µg/kg was given if appropriate. Vasoactive drugs will be administered as needed to maintain circulation. Regular neostigmine (2 mg) and atropine (0.5 mg) will be administered to antagonize neuromuscular blockade at the end of surgery. Postoperatively, the patient will be transferred to the post-anesthesia awakening recovery unit (PACU). For postoperative patient-controlled intravenous analgesia (PCIA), a sufentanil analgesic drug will be used at a rate of 1 µg/kg via both pumps at 2 ml/h, with a single additional dose of 0.5 ml and a lockout time of 15 min.

Follow-up visits will be conducted with registrars who were blinded to group assignment and medication. Data entry for nodal time observation indicators will be completed solely based on the CRF form. The patients’ general condition, such as gender, age, BMI, medical history, height, weight, and AIS score on the night before surgery, will be documented. The heart rate and mean arterial pressure will be measured at four time points: after admission to the operating room (*T*_1_), at the start (*T*_3_), and end (*T*_4_) of surgery, and 30 min after awakening (*T*_5_). The following parameters will be recorded: operative time, anesthesia time, intraoperative blood loss, intraoperative fluid volume, intraoperative dosage of sufentanil and remifentanil, type and dosage of intraoperative vasoactive drug, wake time (time from end of surgery to extubation), and VAS score for resting and coughing 30 min after awakening. All patients will be followed up by a designated person within 72 h after operation. Postoperative sleep quality, sleep duration, and continuity were assessed using the AIS scale and visual analog scale (VAS) score, and analgesic drug doses will be recorded at 24, 48, and 72 h after the operation. Cognitive function will be evaluated using the CAM assessment. Hemoglobin, albumin, serum sodium, testosterone, cortisol, IL-6, TNF, NSE, and Sβ-100 will be measured before surgery, and at 1 and 2 days post-operation.

#### Secondary outcome

Secondary outcomes included postoperative sleep time, incidence of postoperative delirium (POD), VAS pain score, analgesic use and dosage, blood test indexes (hemoglobin, albumin, blood sodium, testosterone, cortisol, IL-6, TNF-α, NSE, and S β-100), and perioperative-related indicators (operation time, anesthesia time, intraoperative blood loss and fluid volume, sufentanil and remifentanil dosage, vasoactive drug type and dosage, and awakening time from the end of the operation to extubation time). The postoperative sleep time was assessed based on the patient's self-reported time of falling asleep to waking up. The CAM method was used for POD diagnosis, requiring positive scores for feature 1 plus 2 and feature 3 or 4 to be considered positive for CAM (Table 2). The use of analgesics and their dosage were recorded.

**Table 2 Tab2:** Confusion assessment method (CAM)

Characteristic	Manifestations
Acute onset and fluctuating course	Whether there is evidence of an acute change in mental status compared with the patient’s basal level
	Whether the patient's (abnormal) behavior fluctuates over the course of 1 day (symptoms are sometimes absent or mild and sometimes severe)
Inattention	Whether patients have difficulty concentrating, such as attention is easily distracted or cannot keep up with the topic being talked about
Disorganized thinking	Whether the patient’s thinking is disorganized or incoherent, such as when the topic of conversation is scattered or irrelevant, thinking is unclear or illogical, or suddenly changes from one topic to another without warning
Altered level of consciousness	Whether the patient’s current level of consciousness is abnormal, such as hypervigilance (excessive sensitivity to environmental stimuli, startle easily), somnolence (drowsiness, easy to wake up), or coma (difficult to wake up)

Scoring criteria: delirium was diagnosed with characteristic 1 plus 2 and characteristic 3 or 4 positive = CAM positive

### Data management and trial oversight

The personal information and records of each participant shall be meticulously preserved in dedicated files and securely stored within a lockable cabinet. Electronic files, safeguarded by password protection, shall rest exclusively on Changhai Hospital’s computer systems. Access to all research data shall be granted solely to authorized members of the research team.

Upon completion of the trial, all participants will receive a comprehensive summary of the research findings as well as information regarding their respective groups. All personal information shall be expunged prior to the public disclosure of the trial results.

Data analysis will be conveyed to an independent Data Monitoring Committee (DMC) with utmost confidentiality, wherein this committee will be tasked with evaluating the cumulative trial data and other pertinent research findings to ascertain the justifiability of recruiting additional participants. It is within their purview to offer suggestions in this regard.

The DMC is scheduled to convene prior to the commencement of the trial and one month after the initiation of participant recruitment, thereafter convening on a monthly basis until the completion of participant enrollment.

Regulatory officials convene monthly meetings to review the conduct of the trial. In accordance with the specific risk assessment of the trial and the documentation in the monitoring plan, on-site monitoring will be conducted. Supervisors will be granted authorization to conduct trial-related monitoring, regulatory inspections, audits, and ethical reviews, while also being provided with direct access to source data/documents.

### Confidentiality

The gathered information will be shared within the project team's secure network drive, overseen by dedicated personnel responsible for data maintenance and privacy protection. Access will be restricted only to members of the experimental team. Participants will be assigned individual trial identification numbers. The experimental data will be published in the form of an article.

### Statistical analysis

We analyzed the data in this study using the statistical software SPSS 26.0. We presented statistical descriptions of the measurement data using either $$\overline{\mathrm{x} }$$±s or median and interquartile range. We performed comparisons between groups using either a two-sample t-test or Mann–Whitney *U* test. We statistically described counting data using rate and constituent ratio. We performed comparisons between groups using either the *χ*^2^ test or Fisher’s exact probability method for pairwise comparisons. We performed comparisons of rank data using the Mann–Whitney *U* test. We analyzed factors associated with POD using logistic regression analysis. In logistic regression analysis, we set α Into as 0.05 and α Out as 0.10. For other hypothesis tests, we considered *P* < 0.05 as statistically significant.

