**Discussion:**

This study aims to investigate the impact of intravenous dexamethasone on sleep quality and duration of patients undergoing robot-assisted radical prostatectomy (RARP). If the findings of this study protocol are affirmative, it could enhance the sleep quality of elderly patients after surgery, thereby minimizing the risk of postoperative delirium (POD), and providing substantial evidence for the perioperative enhanced recovery management of elderly patients.

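### Factors associated with POD are to be selected stepwise by p-value, a rule that readily reports chance factors when many candidates are screened; the between-arm POD test is unaffected

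*Protocol article*

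**What the plan says.** POD is a secondary outcome: "Secondary outcomes included postoperative sleep time, incidence of postoperative delirium (POD), VAS pain score" (Secondary outcome). Two analyses in the Statistical analysis section bear on it.

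- Count data are compared between groups by a chi-square test or by Fisher's "exact probability method for pairwise comparisons". This covers POD incidence by arm.
- A separate model looks for predictors: "We analyzed factors associated with POD using logistic regression analysis". The selection rule follows: "In logistic regression analysis, we set α Into as 0.05 and α Out as 0.10".

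The article does not use the word stepwise. It names no candidate variables and does not say that the randomised arm stays in the model. Among the other secondary outcomes are "blood test indexes (hemoglobin, albumin, blood sodium, testosterone, cortisol, IL-6, TNF-α, NSE, and S β-100". According to Experimental process, these markers are measured before surgery and on days 1 and 2 after it, while pain scores and analgesic doses are recorded up to 72 h. The sample size rests on a sleep score, and no expected POD rate appears anywhere.

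**The concern.** An entry level and a removal level have no function in a model whose terms are fixed in advance. They are the settings of a procedure that adds and drops variables according to their p-values in the trial's own data. Three consequences follow.

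- Each null candidate gets its own chance to enter at 0.05, so the chance of at least one false factor grows with the number screened.
- The p-values and intervals of the final model are computed as if that model had been chosen beforehand, and so overstate the evidence.
- Nothing in the rule protects the randomised arm or excludes variables measured after it. The article's own rationale is that dexamethasone acts through cortisol and inflammation. Postoperative cortisol or IL-6 could therefore lie on the causal path. A blood sample on day 1 or 2 may also be drawn after delirium has begun, so that the marker is a consequence and not a factor.

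At stake is the credibility of any published list of POD risk factors from this trial.

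**Working it through.** **1. The sample available.** Sample size calculating gives Zα = 1.96, Zβ = 1.28, k = 1, means 5.6 and 6.8, and SDs 2.0 and 1.6. Then δ = 1.2 and σ² = (2.0² + 1.6²)/2 = 3.28.

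n = (1.96 + 1.28)² × 2 × 3.28 / 1.2² = 10.4976 × 6.56 / 1.44 = 47.8, so 48 per group.

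48 × 1.2 = 57.6, so 58 per group and 116 in total. This reproduces the plan's 48 before dropout and its final figure: "which would require approximately 58 cases per group and 116 cases in total". None of these inputs concerns POD.

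**2. POD events (assumption).** With no rate in the article, I take 7 to 22 events. That is 7/116 = 6.0% to 22/116 = 19.0% of all patients, or 7/96 = 7.3% to 22/96 = 22.9% if 96 are evaluable.

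**3. Candidates (assumption).** Experimental process and Secondary outcome list about 20 non-laboratory variables, counting treatment, and 9 blood markers at 3 times. Offering everything would mean about 20 + 9 = 29 candidates with baseline markers only, or 20 + 27 = 47 with all times. The article does not say that all would be offered, so I use 10 and 20 as working values.

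**4. Chance of at least one false factor.** For k independent null candidates tested at 0.05, the probability that at least one qualifies is 1 − 0.95^k:

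| k | 10 | 13 | 14 | 20 | 29 | 47 |
|---|---|---|---|---|---|---|
| 1 − 0.95^k | 40% | 49% | 51% | 64% | 77% | 91% |

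Simulation of the rule itself used 116 patients, all candidates null and independent, score-test entry at p < 0.05, likelihood-ratio removal at p > 0.10, and 400 runs per cell:

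| Events | 10 candidates | 20 candidates |
|---|---|---|
| 7 | 36.5% | 60.5% |
| 15 | 31.5% | 60.8% |
| 22 | 36.8% | 62.5% |

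The mean number of false factors was 0.4–0.5 with 10 candidates and 1.0–1.1 with 20. A second simulation used 96 patients, POD in 10% or 15%, a true treatment odds ratio of 0.45, all other candidates noise, and forward entry only. It gave 37.5% and 35.8% with 10 candidates, and 64.3% and 60.5% with 20. The Monte Carlo standard error is about √(0.6 × 0.4/400) = 2.4 percentage points. Together the ranges are about 32–38% and 60–64%.

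**5. Role of the event count.** Reading down the table, the false-factor rate hardly moves between 7 and 22 events. The number of candidates drives it. Few events do a different harm: events per candidate run from 7/20 = 0.35 to 22/10 = 2.2, so coefficients and the selected set are unstable.

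**The case against.** The strongest reply is that the trial's POD comparison does not depend on this model. The chi-square or Fisher test compares arms directly, whereas the logistic regression has another stated purpose. That stands. A reader might infer that the trial has no trustworthy POD treatment comparison, and the article does not support this.

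A reader might also infer that stepwise selection is what loses the treatment effect. In the simulations with 116 patients and POD truly halved (assumed), treatment was absent from the final model in about 86%, 70–73% and 58–60% of runs at about 7, 15 and 22 events. A plain two-proportion test with 58 per arm has power of 14.5%, 28% and 41%, so it would miss the effect in 85.5%, 72% and 59%. The figures match. They show a trial too small for POD, and forcing treatment in would not restore power. It would only ensure that the estimate is reported with its interval.

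Nor do few events cause the false factors (step 5). The candidate count is my assumption: with 10 candidates a false factor is less likely than not, and the rate passes one half only at about 14. The list may sit in a document not shown, and its absence here is no fault. The article does not say that postoperative markers will be offered to the model; the point is only that the rule does not bar them. Finally, the abstract's remark that better sleep could lower POD risk is conditional and is a separate matter from this regression.

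The thresholds themselves survive these objections. They are stated in the text, and an analysis plan would have to contradict the article to remove them.

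**Conclusion.** The point holds in a limited form. The article fixes p-value-driven stepwise selection for its POD factor analysis. If the candidates are null and independent, the rule reports at least one false factor in roughly a third of trials with 10 candidates and about 60% with 20, with p-values that take no account of the search. Correlated candidates or a shorter list would change these rates. Sparse events, which is an assumption because no POD rate is given, add instability. The rule as written leaves open both the loss of the randomised arm from the model and the entry of post-treatment markers, without saying that either will occur.

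The consequence is confined to a secondary, apparently exploratory analysis. The primary sleep outcome and the between-arm POD test are untouched.

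**What to change.** - Delete the entry and removal thresholds.
- Fit one prespecified logistic model for POD with treatment forced in and one or two baseline covariates chosen in advance (for example age). Use Firth penalisation if events are sparse. Two or three parameters on 7–22 events means between 7/3 = 2.3 and 22/2 = 11 events per parameter, so at the low end even this model is thin and one covariate is preferable.
- Admit no covariate measured after randomisation; this excludes postoperative cortisol, IL-6, pain and analgesic use.
- Label the factor analysis exploratory.
- Base any statement about POD on the planned between-arm comparison, reported as a risk difference with 95% CI.

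The cost is a change of analysis wording. No patients, visits or measurements are affected. The sponsor gives up a data-selected list of risk factors.

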## Discussion

This study protocol follows a single-center, randomized, double-blind, placebo-controlled design. Our objective is to investigate the potential of administering dexamethasone during anesthesia induction to improve postoperative delirium in elderly patients undergoing robot-assisted radical prostatectomy (RARP), enhance sleep quality, and ultimately facilitate enhanced recovery after surgery (ERAS).

It has been shown that prostate cancer is a prevalent urinary tract neoplasm among elderly men, and early surgical intervention is the primary treatment modality [17]. In recent years, minimally invasive surgery techniques, such as robotic-assisted radical prostatectomy (RARP) and laparoscopic radical prostatectomy (LRP), have become increasingly popular, replacing traditional open surgery. However, despite its advantages over traditional surgery, RARP has not significantly reduced many of the anesthesia-related complications associated with surgery. Common postoperative problems among elderly patients undergoing RARP include pain, nausea, vomiting, sleep disturbance, and cognitive decline. Of these, sleep disturbance is particularly prevalent among the elderly and has not been effectively addressed to date.

Research has demonstrated that dexamethasone is an artificially synthesized corticosteroid with potent anti-inflammatory effects, that reduces cortisol secretion before stress stimulation via negative feedback inhibition of the hypothalamus–pituitary–adrenal cortex axis. This reduces the negative effects caused by surgical stress to some extent [18]. Other studies have indicated that preoperative administration of dexamethasone may lower the incidence of POD [12]. Additionally, some studies have reported that elevated serum cortisol levels in the early postoperative period are linked to a heightened risk of cognitive impairment [7, 13]. Therefore, the intravenous administration of dexamethasone during anesthesia induction theoretically has the potential to reduce the release of inflammatory mediators, attenuate the inflammatory response, decrease perioperative cortisol secretion, improve patient sleep quality, and reduce the incidence of postoperative delirium (POD).

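### One flat P < 0.05 rule declares significance for at least 13, plausibly about 30, unranked secondary comparisons, although delirium is in the title and objective

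*Protocol article*

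**What the plan says.** The decision rule is in the last sentence of Statistical analysis. After entry and removal levels for the logistic regression, it reads: "For other hypothesis tests, we considered *P* < 0.05 as statistically significant". No order of testing, division of alpha or exploratory label follows.

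The Secondary outcome section gives one undivided list: "Secondary outcomes included postoperative sleep time, incidence of postoperative delirium (POD), VAS pain score, analgesic use and dosage, blood test indexes", of which there are nine, followed by perioperative indicators such as operation time, blood loss and drug dosages. Experimental process adds repetition. The nine blood indexes are measured on postoperative days 1 and 2, analgesic doses are recorded at 24, 48 and 72 h, and pain is scored at rest and on coughing 30 minutes after awakening.

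Delirium is one item in that list. It is also in the article's title, in the aim that closes the Background, and in the Discussion: "Our objective is to investigate the potential of administering dexamethasone during anesthesia induction to improve postoperative delirium in elderly patients". The abstract's Discussion says that affirmative findings could improve sleep, "thereby minimizing the risk of postoperative delirium (POD), and providing substantial evidence for the perioperative enhanced recovery management of elderly patients".

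The primary outcome is sleep quality on the AIS at 24 and 48 h.

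**The concern.** The rule does not separate a result that may support a claim from one that only describes. Under it, a difference in delirium, pain, cortisol or serum sodium with P = 0.04 is statistically significant in the same sense as the primary result. With many comparisons, some chance findings can be expected, and the text gives no basis for discounting them.

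Delirium matters most. The article treats it as something the trial is meant to answer, yet its place in the testing scheme is that of any other secondary outcome. The stated mechanism is that delirium improves through better sleep, but nothing links a delirium claim to the primary result. The abstract's wording could also let a delirium benefit be inferred from the sleep result without reference to the delirium comparison.

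**Working it through.** **The plan's own figure.** The article states no error rate for the secondary outcomes as a group. Its alpha appears in the sample size section: "The significance level (*α*) was set at 0.05 and the power (*β*) at 0.10", two-sided with Z = 1.96, applied to one score: "The control group had a score of 5.6 ± 2.0 while the 10 mg dexamethasone group had a score of 6.8 ± 1.6". With σ² = (2.0² + 1.6²)/2 = 3.28 and δ = 1.2:

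n = (1.96 + 1.28)² × 2 × 3.28 / 1.2² = 10.4976 × 6.56 / 1.44 = 47.8, so 48 per group.

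This matches the article. The design alpha is therefore two-sided 0.05 for a single comparison, and the secondary outcomes play no part in the calculation.

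**Counting the comparisons** (from Secondary outcome and Experimental process):

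| Outcome | One test each | Separate time points |
|---|---|---|
| Sleep time | 1 | 3 (24, 48, 72 h) |
| Delirium | 1 | 1 |
| VAS pain | 1 | 5 (rest and cough at 30 min; 24, 48, 72 h) |
| Analgesic use/dose | 1 | 3 (24, 48, 72 h) |
| Nine blood indexes | 9 | 18 (days 1 and 2) |
| **Total** | **13** | **30** |

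The second column assumes a separate test at each time point, which the article does not say. Nine perioperative indicators would bring it to 39. They are left out because they are largely process measures on which no efficacy claim is placed.

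**Chance of at least one P < 0.05 in either direction, all nulls true.** For m independent tests it is 1 − 0.95^m:

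- m = 13: 1 − 0.95¹³ = 0.487
- m = 30: 1 − 0.95³⁰ = 0.785

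For an assumed common correlation r, with c = 1.96 and u standard normal, it is

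1 − E_u[{Φ((c − √r·u)/√(1−r)) − Φ((−c − √r·u)/√(1−r))}^m].

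**Benefit direction only.** Each test has a one-sided level of 0.025. Under independence the chance is 1 − 0.975^m; otherwise the lower-limit term is dropped from the expression above. All tests are taken as oriented so that positive correlation runs in the benefit direction.

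| m | Direction | r = 0 | r = 0.5 | r = 0.7 |
|---|---|---|---|---|
| 13 | either | 49% | 33% | 24% |
| 30 | either | 79% | 51% | 34% |
| 13 | benefit | 28% | 17% | 12% |
| 30 | benefit | 53% | 25-26% | 17% |

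The expected number of two-sided false positives does not depend on r: 13 × 0.05 = 0.65 and 30 × 0.05 = 1.5.

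**The case against.** **An analysis plan may settle this.** Ordering and exploratory labels are often left to a statistical analysis plan, and the article says that a fuller protocol exists. If the article were silent, this would dispose of the point. It is not silent: it states a rule for all remaining tests, and a later plan that ordered or downgraded the secondaries would have to override it.

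**A hierarchy already exists.** Sleep quality is primary, the sample size rests on one score, and secondary outcomes are conventionally read as supportive. The article also claims no family-wise rate for them, and each single test does have a nominal 5% level. All of that stands. What is missing is any order among the secondaries, or any link from delirium to the primary, in a text that makes delirium a headline objective.

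**A reader might infer that a false secondary effect is more likely than not, or that the trial will probably report a false benefit.** The documents do not support either as a general statement. In either direction, the probability stays below one half for 13 tests at every correlation considered, and for 30 tests it falls to 34% at r = 0.7. In the benefit direction it is about 17% to 26% at r = 0.5. A total of 39 would need the process measures and a separate test at every time point. Some nulls may also be false on the article's own reasoning, since dexamethasone is expected to lower cortisol.

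**A reader might infer that the trial means to claim delirium after a failed primary.** No section says so. The abstract's sentence is conditional on affirmative findings and derives the delirium benefit from better sleep. The rule permits such a claim without planning it. A single delirium test also carries only its nominal 5%, so the group-wide figures do not measure the risk of a false delirium finding.

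**Conclusion.** The point holds in a limited form. The Statistical analysis section fixes a significance rule too broad for the outcomes it covers, and delirium has no defined inferential role although it is in the title and objective. With all nulls true, at least one nominally significant secondary result would arise with probability 24-49% (13 tests) or 34-79% (30 tests), and in the benefit direction 12-28% or 17-53%.

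These figures rest on a derived count, an assumed exchangeable correlation from 0.7 to 0, and the complete null. They show the scale of the problem and do not forecast what the trial will report. The primary analysis and the sample size are unaffected.

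**What to change.** First define primary success across the two AIS assessments (24 h and 48 h), because any condition based on the primary result is undefined until that is done. Then replace the last sentence of Statistical analysis with wording such as:

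*Two-sided P < 0.05 supports a confirmatory claim for the primary AIS comparison, with success across 24 h and 48 h as defined above. Incidence of postoperative delirium is the key secondary outcome and is claimed as confirmatory, at two-sided 0.05, only if the primary comparison succeeds. All other secondary outcomes, including blood indexes at each time point and perioperative indicators, are exploratory. They are reported as between-group differences with 95% confidence intervals, without a declaration of significance.*

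Reword the abstract's Discussion so that any conclusion about delirium rests on the delirium comparison itself and is not inferred from the sleep result.

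The cost is wording only. The total of 116 patients and the data collected stay as they are. The downside is small: delirium cannot be claimed as confirmatory if the primary fails, and pain and biomarker results remain exploratory whatever the primary shows.
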